## Abstract

**Background:**

Nigeria presently has the second highest absolute number of maternal deaths and perinatal deaths (stillbirth and neonatal deaths) in the world. The country accounts for up to 14% of global maternal deaths and is second only to India in the number of women who die during childbirth. Although all parts of the country are worsened by these staggering statistics, several lines of evidence show that most maternal, and perinatal deaths occur in the north-east and north-west geo-political zones where women have limited access to evidence-based maternal and neonatal health services. The proposed project intends to identify the demand and supply factors that prevent women from using PHCs for maternal and early new-born care in Nigeria, and to test innovative and community relevant interventions for improving women’s access to PHC services, and thus, ultimately, to prevent maternal and perinatal deaths.

**Methods:**

An open-labelled, randomized controlled trial will is carried out in two local government areas selected based on three criteria (i) maternal mortality rates (ii) PHC utilization rates and (iii) and geographic localization. The study will be conducted over 54-months in six communities, with PHCs in six communities of similar status serving as control sites. Surveys about quality of care and maternal health services utilization will be carried out at baseline, at midterm and at end of the project to test the effectiveness of the intervention, alongside conventional epidemiological measures of maternal and perinatal mortality. Ethical approval for the study has been granted (reference no. NHREC/01/01/2007). The findings will be published in compliance with reporting guidelines for randomized controlled trials.

**Discussion:**

The current Federal Government in Nigeria has identified PHC as its main strategy for increasing access to health in Nigeria. However, despite numerous efforts, there are persisting concerns that there is currently no scientific evidence on which to base the improvement of PHCs. The results of this study will identify barriers in the use of PHCs and will provide scientific evidence for effective and innovative interventions for improving PHCs that can be rolled out throughout the country.

**Trial registration:**

Clinical Trials.gov NCT02643953.

## Background

Current estimate of maternal mortality in Nigeria is 545 to 608 per 100,000 births [1, 2], which is among the highest in the world. Nigeria was listed in a Lancet publication as one of six countries accounting for 50% of global maternal deaths [2]. The estimated 40,000 maternal deaths in the country are the world’s second highest, and together with India, accounts for one-third of all maternal deaths worldwide. Nigeria’s stillbirth rate is 42 per 1000 and the second highest in the world, and is one of ten countries that account for up to 66% of stillbirths globally [2]. The World Health Organization (WHO) recommends increased access by women to evidence-based maternal and perinatal health care (antenatal, intrapartum and early postnatal care) as an essential intervention for improving maternal and perinatal outcomes in low-income countries [3–5]. This has been borne out by data showing that countries with the highest rates of skilled maternal health attendance also have the best indicators of maternal and perinatal health, even after controlling for other parameters of development [6–8].

Primary Health Care (PHC) is the recommended route for improving access to Skilled Birth Attendance (SBA) in low-resource settings. Several studies indicate that the major reasons that women fail to use maternal health services at PHCs are lack of money to pay for health services, difficulty with transportation, perceptions relating to the negative attitudes of health workers, and lack of permission from husbands and other family members [9–13]. A report of a Nigerian Presidential Committee titled “Accelerating the Attainment of MDG 5” in 2006 [14] identified high rate of poverty and the inability to pay for health services as major barriers experienced by women in accessing safe maternal care. To solve financial barriers, the Federal Ministry of Health in 2007 [14–19] recommended that State governments (the second tier of government in Nigeria) should implement policies on provision of free maternal and child health services. The Nigerian Primary Health Care Development Agency (NPHCDA) also established the Midwives Services Scheme (MSS) [16] for the purpose of staffing PHCs in under-served areas for the provision of maternal health care to address the supply challenges of lack of professionals in maternal health centres in many parts of the country. The results showed that by 2010, up to 18 out of the 36 Nigerian States were offering free maternal and child health services [17, 18]. In December 2012 [16], the NPHCDA reported that about 2500 midwives had been employed to work in PHCs in rural under-served communities across the country.

Despite the provision of free maternal care services, the experience in many states has been that health care utilization initially increased in some states, but this has not been sustained over time. Many health providers and women voiced concern that despite the free services, many health facilities lacked basic facilities, the health care personnel were poorly motivated, while many of the pre-existing challenges that led to poor utilization remained [19, 20]. The exception was Ondo State, which witnessed sustained and unparalleled transformation of maternal care, with the State achieving MDG-5 status, the only state to do so in the country. This was due to the institutionalisation of the *Abiye* program [21, 22]*,* which addressed both the demand and supply factors contributing to access barriers in a composite and multi-faceted manner. Under Abiye, the government provided free antenatal and delivery care, linked pregnant women to health providers through mobile phones and improved clinical service delivery at secondary health facilities. However, the fact that this intervention focussed on secondary care facilities (first referral level) only and was mainly located in urban areas without a research strategy to compare results with control sites diminished the policy relevance of this approach.

Evidence abounds to show that unskilled delivery dramatically increases the risk of maternal and perinatal death, as women who die during pregnancy, or who experience perinatal deaths, are often those not receiving antenatal, intrapartum and postnatal care, and those whose deliveries are attended by an unskilled birth attendant or who deliver at home [20–22]. National data from the Demographic and Health Survey [23] indicate that less than 65% of Nigerian women receive antenatal care during pregnancy, less than 33% are attended to by skilled birth attendants (SBA) at the time of delivery, and under 40% receive follow-up postnatal care.

In 2007, the Federal Ministry of Health developed and launched the Integrated Maternal, Newborn and Child Health (IMNCH) policy [24], to promote health equity for women and children. This policy emphasizes the provision of quality care for women right from the time of conception through pregnancy and the immediate postnatal period. Ensuring access to quality services for marginalised women was its focus, which the Ministry identified as the main operating framework of the document. To ensure that this policy can aid the most marginalized women in Nigeria, the Ministry adopted Primary Health Care as its main route of implementation. Nigeria’s health care system is based on a 3-tier system: Primary Health Care (PHC) as the entry point; Secondary Care (regional/general hospitals) as the first referral level; and Tertiary Care (teaching hospitals) as the second level referral. PHC is the most accessible and affordable form of care that serves most of the population, leaving substantially fewer women in need of Secondary and Tertiary care.

Nigeria presently has about 34,000 PHCs covering all the health wards (comprising population areas of 10,000 to 30,000 persons) and most rural and hard-to-reach communities. By contrast, the country has fewer Secondary Health Centres and Teaching Hospitals located mainly in large cities and urban areas. By focussing on the primary health system for implementing IMNCH, the idea is to reach the many poor and rural women at highest risk of maternal and perinatal mortality. Many such women can be effectively managed at PHCs, while the few who require more complex care (e.g. caesarean delivery or neonatal intensive care) would be transferred to higher level emergency care centres through the development of an effective referral system.

Despite a thoughtful system designed to reduce maternal and perinatal mortality in Nigeria, this goal has yet to be achieved among its most vulnerable and marginalized women. Many women still do not use PHCs for maternal and neonatal care, with a large proportion opting to use traditional forms of care or self-care. The problem has been compounded by PHCs that are inadequately staffed and equipped. Many PHCs are not aware of the updated guidelines for the management of pregnant women and neonates, and some PHCs are inadequately linked to secondary and tertiary care centres, for advice or patient transport. If the PHC system is to contribute effectively to reducing maternal and perinatal deaths in Nigeria, both the demand and supply sides of the system must be improved and strengthened. Women must be encouraged and empowered to use the PHC for maternity and early postnatal care. The PHCs must be improved and made more functional.

Despite the consensus of all stakeholders in Nigeria that the primary health care system is the key to reducing maternal and perinatal mortality, steps have yet to be taken to consolidate and revamp the system. In 2010, the Nigerian Primary Health Care Development Agency (NPHCDA) launched the Midwifery Services Scheme (MSS) to ensure the deployment of midwives to poorly staffed PHCs throughout the country. However, to date, the MSS has only attained modest success, while the questions regarding how to make the system work effectively and how to attract women to use the services still remain to be addressed. The National Assembly is currently debating a bill that will ensure that at least 1% (1 %) of Nigeria’s annual budget is allocated to improve the functioning of the PHC system. However, unless practical methods are in place for improving both the delivery of PHCs and the access of women to PHCs, greater funding alone will not achieve the desired results. The proposed project intends to identify the demand and supply factors that prevent women from using PHCs for maternal and early new-born care in Nigeria, and to test innovative and community relevant interventions for improving women’s access to PHC services, and thus, ultimately, to prevent maternal and perinatal deaths.

## Methods

### Theoretical framework

Three conceptual frameworks are considered in this study. The first is the three-delay model, earlier proposed by Thaddeus and Maine [19]. In brief, the model describes the interlinking nature of the different factors that prevent women from accessing evidence-based maternal and perinatal health care. The model identifies the different barriers that women face in achieving the care needed to prevent maternal and neonatal complications. This model identifies Type 1 Delay is the failure of a woman to seek help when she experiences pregnancy complications, while Type 2 Delay is delay due to difficulties with transportation to a health facility. By contrast, Type 3 Delay is the delay experienced when the woman arrives in the health facility.

The decision to use maternal health services is largely an individual choice, while the utilization of health services remains a complex and multi-facetted behavioral phenomenon. Thus, our second conceptual framework for this study is based on the *health seeking behavior model* developed by Anderson and Newman [25]. This model proposed that the use of health care services is a function of three sets of individual characteristics – predisposing characteristics, enabling characteristics and need characteristics. The model posits that the use of maternal health services is influenced by predisposing factors such as maternal age, education, household size, number of previous pregnancies and health related attributes. With respect to enabling characteristics, the framework proposes that access to health services and health personnel is an important determinant of maternal health care utilization. This implies that women’s ability to use maternal health facilities will depend on the availability of such facilities and their possession of the means to access the facilities. An important component of this framework – the need component – suggests that the use of maternal health services can be influenced by a woman’s perception of the relative importance of modern health care services versus traditional methods of care. Added to this is a woman’s perception and understanding of pregnancy complications and her desire to deliver safely and attain a healthy newborn baby.

In this proposed project, we will use a simplified definition of access to health services, as proposed by Peters et al. [26] who defined it as “the timely use of service according to need”. Therefore, a third conceptual framework that exemplifies this study is the four dimensions of access proposed by O’Donnell [27]. This includes availability, geographical accessibility, affordability and acceptability, while he further proposed that these could stem from both demand and supply sides. *Demand side* factors are those that relate to the ability to use maternal health services at individual, household or community levels. *Supply side* factors relate to the health care system that hinder service uptake by individuals, households and communities. In this regard, some demand side factors include costs of services (such as indirect costs related to transportation), information on health care services/providers, education, household expectations, community and cultural preferences.

We hypothesize that if we can reduce Type 1, 2 and 3 Delays, then we can reduce maternal and perinatal mortality and morbidity, especially if demand and supply side factors are addressed concurrently. Thus, this project aims to find out why delays occur in seeking maternal health care in PHCs, and then to test interventions to reduce all types of delays. We will also ensure that the tested interventions focus on most at-risk poor women in rural, urban and peri urban areas that use PHCs for antenatal, intrapartum and early postnatal care.

We will do so by generating new evidence, and complimenting those findings with the existing evidence about improving maternal health care delivery in low and middle-income countries. The project will be designed to maximize community participation and ownership. By having community members lead the intervention design and implementation, there is a better chance of improving women’s use of PHCs for maternal care in differing regions of Nigeria.

### Study design and setting

A community-based, multi-site, and multi-disciplinary cluster randomized trial using a mixed methods approach will be used. The project will be done in three phases: A formative phase (Phase 1) and an intervention phase (Phase 2), followed by evaluation of the intervention and policy transformation of the findings (Phase 3). The study will be conducted over 54-months in selected intervention communities, with selected communities of similar status serving as control sites. Surveys about maternal health services utilization will be carried out at baseline, at midterm and at end of the project to test the effectiveness of the intervention, alongside conventional epidemiological measures of maternal and perinatal mortality, each also collected in the three terms (Table 1).

**Table 1 Tab1:**
[figure not shown]
Project GANTT chart

### Research objectives

This project aims to reduce maternal and perinatal mortality in Nigeria by strengthening the availability and use of maternal primary health care services by vulnerable women.

The specific objectives of the project are as follows:To identify the demand and supply factors responsible for use and non-use of primary health care for maternal health in selected communities in Edo State, Nigeria;Based on Objective 1, to derive and implement a set of multi-faceted community-led interventions to increase women’s access to antenatal, intrapartum and postnatal care services in primary health centres in six (6) randomly selected communities in six geo-political zones of the country;To evaluate the effectiveness of the implemented multi-faceted interventions by comparing both indicators of access to services, as well as maternal and foetal/new-born health outcomes, between the intervention-receiving communities vs. the control communities not receiving the intervention;To use the study findings to modify Nigerian policy and programmes aimed at increasing women’s access to evidence-based maternal and neonatal services, especially within the country’s rural areas.

### Key research questions

The relevant questions that would be addressed by the study include the following:What demand factors (acceptability, geographical accessibility, affordability etc.) account for the low utilisation rates of evidence-based prenatal and intrapartum care services within PHCs located in rural communities within Edo State, Nigeria?What supply factors (healthcare providers, availability of medical equipment, essential drugs and infrastructure etc.) account for the low utilisation rates of evidence-based prenatal and intrapartum care services within PHCs located within rural communities in Edo State, Nigeria?How do these demand and supply factors interact with each other?What are women’s preferences for specific maternal health service delivery?What are communities’ perceptions about maternal health and illness, including the possibility of death in pregnancy, and how do these beliefs and perceptions impact the use of evidence-based maternal health services by community constituents?How do we develop community understanding and acceptance of the need to build women’s agency and capacity in accessing PHCs for maternal health?What support can indigenous communities provide for women seeking maternal health services during pregnancy?What types of interventions are effective in increasing the use of evidence-based prenatal and intrapartum care services in Edo State, Nigeria?What is the best model for communicating the study results to policymakers?What are the best ways to ensure that policy makers will use the study results and devote resources for improving MNCH indicators?

### Study area

Nigeria currently has a population of over 180 million, making it the sixth largest in the world after China, India, USA, Indonesia and Brazil. Nigeria is made up of 36 States and a Federal Capital Territory and has 774 Local Government Areas (LGAs). It is grouped into six geo-political zones/regions: North West, North East, North Central, South East, South West and South- South. The project is being conducted in two LGAs in Edo State, which we hope to scale up to other health care centres in the State and the country at large. Edo State is one of the 36 States of Nigeria with the population of over 3 million and total land area is 19,794sq.km. The study is being conducted in Esan South East and Etsako East LGAs in Edo State, South-South region of Nigeria. Both LGAs are located in the rural and riverine areas of the state, adjacent to River Niger, with Estako East in the northern part of the Edo State part of the river, while Esan South East is in the southern part. Administratively, each LGA comprises of 10 political wards and there are several communities in each ward (total of 100 communities from Esan South East and 42 from Etsako East). The two LGAs have a total population of 313,717persons, with Esan South East accounting for 167,721 and Etsako East LGA accounting for 145,996.

### Study phases

#### Phase 1: Formative research

##### Quantitative method

The quantitative instruments (individual woman, exit interview and site inventory assessment questionnaires) will be entered into a computer-assisted personal interviewing (CAPI) program. This method will explore the supply factors in the use or non-use of maternal health care services. A probabilistic sample will be carried out in the 20 communities to be selected out of a total of 142 communities in both LGAs, and will have two phases. In the first phase, 10 communities (5 PHC owned and 5 non-PHC owned communities) in each of the two LGAs will be chosen. All ever-married women aged 15 to 45 in each household to be visited who have an under-5 children will be eligible for interview to determine whether they have given birth within the period, and if so whether they have used the services of the PHC. This will continue until the required sample size of about 1450 women is achieved taking at least 72 women from each community. In addition, exit interview will be conducted in up to 10 selected health facilities with clients who would have received antenatal care, delivery or post natal care, to assess patients’ satisfaction through quality of care, patients’ time of travel or distance to facilities, and the cost of services at the PHCs.

In the second phase, PHCs/facilities assessment will be done through a checklist developed using the National Primary Health Care Development Agency standard. This will be used to assess the quality of infrastructural facilities, availability of clinical services through medical equipment and essential drugs as well as the availability of health care providers. All quantitative instruments will be designed and pre-tested to ensure that they are consistent to sufficiently answer related research questions.

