### Data source and sampling

A combination of secondary and primary data is required for the study. The sample size formula below is applied for the formative research survey as follows:

n_1_ = {[p_1_q_1_ + p_o_q_o_]) (Z_α/2_ + Z_β_)^2^}/ (p_1_-po)^2^.

p_0_ = utilization of PHC for maternal and perinatal in the control arm (assumed to be − 5 reduction in the prevalence in the experiment site).

p_1_ = utilization of PHC for maternal and perinatal care in the experimental arm.

*z*_*α*_ = Two-sided standard normal variate at 95% level of significance = 1.96.

*z*_*β*_ = Statistical power at 80% = 0.84;

n_1_ = n_2_.

n_1_ = no of study participants in the experimental group.

n^2^ = no of study participants in the control group.

We assume 50% since there is no literature from the geographical location of the study which reported the prevalence of utilization of PHCs for maternal and perinatal health care. Thus;

n^1^ = (0.50 × 1–0.50 + 0.45 × 1–0.45) (1.96/2 + 0.84)^2^/(0.50–0.45) 2.

(0.25 + 0.2475) (3.3124)/0.0025.

n^1^ = 659.

n^2^ = 659.

Total sample size = 1318.

10% adjustment for non-response = 132.

Total = 1450.

There will be 725 respondents in the experiment LGA and 725 in the control LGA.

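### The only sized survey spreads 725 women per arm over 20 communities, half without a PHC, but the trial compares six communities with six

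*Protocol article*

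**What the plan says.** Four places in the protocol article bear on this.

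- **Phase 1, Quantitative method.** The survey is done in "20 communities to be selected out of a total of 142 communities in both LGAs", and "10 communities (5 PHC owned and 5 non-PHC owned communities) in each of the two LGAs will be chosen". That makes 10 communities with a PHC and 10 without. The target is about 1,450 women, "taking at least 72 women from each community".
- **Data source and sampling.** The formula is introduced as applying to the formative survey, but it is a two-arm comparison of PHC use (50% v 45%) with 80% stated power. It ends: "There will be 725 respondents in the experiment LGA and 725 in the control LGA".
- **Abstract, Methods.** "The study will be conducted over 54-months in six communities, with PHCs in six communities of similar status serving as control sites".
- **Research objectives, objective 2.** The intervention is placed "in primary health centres in six (6) randomly selected communities".

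Study design and setting adds: "Surveys about maternal health services utilization will be carried out at baseline, at midterm and at end of the project". Their stated purpose is to test effectiveness. No passage says whether the Phase 1 survey is the baseline survey, or how the 12 trial communities relate to the 20 surveyed ones. The statistical analysis plan section judges baseline comparability between LGAs, not between communities.

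**The concern.** The sample size treats the 20 surveyed communities as if they were the two arms of the trial. The trial description has 12 communities, and its wording points to communities with a PHC, of which the survey includes only 10. Twenty communities cannot be the 12, and 10 PHC communities cannot contain 12.

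The consequence depends on which comparison is meant. If six communities are compared with six, the stated 725 per arm is not available to that comparison. If one LGA is compared with the other, women from communities that are not intervention sites enter the experiment arm and may dilute the effect. These are alternative harms and do not add up. Under either, 725 v 725 does not describe the women who inform the contrast between intervention and control sites.

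**Working it through.** **Inputs from the protocol article.** 20 surveyed communities, 10 with a PHC; 1,450 women; six intervention and six control communities (Abstract); p1 = 0.50, p0 = 0.45; z = 1.96 and 0.84.

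**1. The plan's own figure.** n per group = (0.25 + 0.2475) × (1.96/2 + 0.84)² / 0.05² = 0.4975 × 3.3124 / 0.0025 = 659. Doubled, 1,318; plus 132 for non-response, 1,450. Over 20 communities this is 1,450/20 = 72.5 women each, which agrees with the minimum of 72. So 1,450 is the 20-community total. (It reproduces only with 1.96 halved. That is a separate matter, but it means power is already below 80% at the stated size.)

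**2. Overlap of the frames, six v six.**

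| | Most trial communities that can be surveyed | Fewest surveyed communities outside the trial | Women outside (× 72.5) | Women per arm |
|---|---|---|---|---|
| Trial sites may lack a PHC | 12 of 12 | 20 − 12 = 8 | 580 (40%) | 6 × 72.5 = 435 |
| Trial sites must have a PHC | 10 of 12 | 20 − 10 = 10 | 725 (50%) | 5 × 72.5 = 362.5 |

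The last column assumes an even split between arms. At exactly 72 women per community the per-arm figures are 432 and 360.

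**3. Power for 50% v 45%.** Two-sided 5%, individual level, no clustering: power = Φ(0.05/√(0.4975/n) − 1.96).

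- n = 725: 0.05/0.0262 = 1.909; Φ(−0.05) = 48%.
- n = 435: 0.05/0.0338 = 1.478; Φ(−0.48) = about 31%.
- n = 362.5: 0.05/0.0370 = 1.350; Φ(−0.61) = 27%.

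The loss due to the frame is from 48% to 27–31%. The gap between 80% and 48% comes from the halved 1.96.

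**4. LGA v LGA.** All 1,450 women are inside. Of the 10 surveyed experiment communities at most 6 can be intervention sites, or 5 if these must have a PHC. With no reach beyond those sites and equal numbers per community, the expected difference is 5 × 6/10 = 3.0 or 5 × 5/10 = 2.5 points. At 725 per arm, with p0 = 0.45:

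- 3.0 points: 0.03/0.0262 = 1.146; Φ(−0.81) = 21%.
- 2.5 points: 0.025/0.0262 = 0.955; Φ(−1.01) = 16%.

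With full reach across the experiment LGA there is no dilution, and power stays at 48%. The range is therefore 2.5 to 5 points.

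**The case against.** The strongest defence is that Phase 1 is formative research and not the trial. Objective 1 asks about use and non-use of PHCs, so sampling communities without one is sensible, and a journal article may leave the midterm and endline sampling to the full protocol. The first part stands: including non-PHC communities is no flaw in a formative survey. It does not remove the conflict, because the article itself sizes this survey as experiment v control and allots every woman to an arm. It is also the only sample size given.

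A reader might infer that at least two trial communities will have no baseline. The article does not establish that. It would require that Phase 1 is the only baseline, which is never stated (the Gantt chart that might settle it is not shown), and that all 12 sites have a PHC, which is suggested but not said. If non-PHC sites are allowed, all 12 could lie within the 20.

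A reader might also take 2.5 to 3.0 points as the expected effect. That is the zero-reach extreme. The intervention design includes PHC outreach, home follow-up by community health rangers and referral by traditional birth attendants, and the Background describes PHCs as serving wards. Women in non-PHC communities may well be reached, with less dilution.

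Finally, the count of six control communities appears only in the Abstract, and the root of the problem is that the unit of allocation, LGA or community, is unclear. Both points are fair. They mean that the passages must be reconciled, not that the counts agree.

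**Conclusion.** The passages conflict, and the stated 725 per arm cannot serve a six v six comparison. Under that comparison 40% to 50% of the surveyed women, at a minimum, are outside it. About 360 to 435 per arm remain, with about 27% to 31% power against about 48% at 725, all before clustering. These figures assume about 72 women per community, the largest possible overlap of the two frames, and an evaluation survey that uses the Phase 1 frame.

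Only if Phase 1 is the sole baseline and every trial site has a PHC does it follow that at most 10 of 12 trial communities can have baseline data.

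Under an LGA v LGA comparison no woman is outside, but up to half of a 5-point effect could be lost, depending on reach beyond the intervention sites.

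**What to change.** Reconcile the Abstract, objective 2, the Quantitative method section and the Data source and sampling section. State the unit of allocation, whether the Phase 1 survey is the baseline, and whether every trial site has a PHC. Then fix the 12 trial communities before sampling, draw the baseline, midterm and endline evaluation samples from them, and leave communities outside the 12 out of the effect estimate. The same 1,450 interviews give 1,450/12 = about 121 women per trial community.

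If the 20-community frame is kept, restate the per-arm size and power for the women who are actually in trial communities.

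The change is cheap before fieldwork, but it is not free. With 1,450 interviews in total, any non-PHC sample kept for objective 1 takes the trial communities below 121 each. Keeping all 10 non-PHC communities at 72.5 women, for example, would leave 725/12 = about 60 per trial community. The alternative is to fund extra interviews.

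### Requiring an under-5 child leaves some bereaved mothers out of the Phase 1 household survey and modestly overstates use of care

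*Protocol article*

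**What the plan says.** Under Phase 1, Quantitative method, the article fixes who may be interviewed: ever-married women between 15 and 45 "in each household to be visited who have an under-5 children will be eligible for interview". The same sentence gives the purpose of the interview: "to determine whether they have given birth within the period, and if so whether they have used the services of the PHC". The group of interest is thus women with a recent birth, while the entry condition is having a young child.

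Three other places bear on the point:

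- **Background.** Of women who die in pregnancy "or who experience perinatal deaths, are often those not receiving antenatal, intrapartum and postnatal care". The same section says that Nigeria's "stillbirth rate is 42 per 1000".
- **Data source and sampling.** The sample size is tied to Phase 1: "The sample size formula below is applied for the formative research survey as follows". It is nevertheless split by arm: "There will be 725 respondents in the experiment LGA and 725 in the control LGA".
- **Study design and setting, and Research objectives.** "Surveys about maternal health services utilization will be carried out at baseline, at midterm and at end of the project to test the effectiveness". Perinatal mortality is listed next to these surveys as a separate set of measures. Objective 3 compares access indicators "as well as maternal and foetal/new-born health outcomes" between intervention and control communities.

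**The concern.** A woman who delivered a stillborn baby, or whose baby died, had a pregnancy, a delivery and a choice of where to seek care. If she has no other child under five, the rule leaves her out. Screening on a child does not help to find recent births. Among women with a birth in the period, it removes only those left with no young child. By the article's own account, such women are often the ones who went without care.

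Two things are at stake. The first is the formative result. Use of primary health centres and SBA would read too high, and the analysis of non-use would lack some of the women whose experience matters most for designing the intervention. The second is conditional. If midterm and end surveys use the same rule, entry to the sample depends on child survival after allocation, which the intervention is meant to improve.

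**Working it through.** The plan gives no figure for this effect, and its total of 1,450 does not depend on it. The question is how large the selection effect can be.

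**Inputs from the article**

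- Stillbirths: 42 per 1,000 (Background, national).
- SBA: below 33% (Background, national survey). I use s = 0.33.
- Planning contrast: 50% against 45% use, a difference of 5 points (Data source and sampling).

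**Assumptions, not in the article**

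- Neonatal deaths: 20 to 40 per 1,000. Added to stillbirths, losses are L = 6.2% to 8.2% of births.
- Losses are RR = 2 to 3 times as frequent without skilled care.
- The share e of losses whose mother has no other under-5 child is 15–22% of all losses in a five-year window, or 34–48% if only the most recent birth counts. These shares come from simulated birth histories: women 15–45, first birth at about 20, mean interval 30–36 months, 22 months after a loss, and loss up to 1.5 times higher at first birth. I apply e equally to losses with and without skilled care.

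**Level of SBA**

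Loss risk with skilled care: x = L / (s + (1 − s)RR).

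SBA among births whose mothers are eligible: s(1 − e·x) / (1 − e·L).

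- Low end (L = 0.062, RR = 2): x = 0.062/1.67 = 0.0371.
- High end (L = 0.082, RR = 3): x = 0.082/2.34 = 0.0350.

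| Share of losses excluded | Low end | High end | Overstatement (points) |
|---|---|---|---|
| All births (e = 0.15; 0.22) | 33.12% | 33.35% | 0.12 to 0.35 |
| Most recent birth (e = 0.34; 0.48) | 33.29% | 33.77% | 0.29 to 0.77 |
| Every loss (e = 1) | 33.9% | 34.7% | 0.9 to 1.7 |

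The last row is an upper bound, because mothers with another under-5 child remain eligible.

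**Sensitivity at the plan's 50% use**

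Let f be the share of women with a recent birth who are excluded, and r their use relative to eligible women. The overstatement is 0.50 × f × (1 − r).

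- Stillbirths only, every loss excluded (f = 0.042): 2.1 points at r = 0 and 1.05 at r = 0.5.
- Stillbirths only, 30–60% of bereaved mothers with no other under-5 child, r = 0.5: 0.3 to 0.6 points.
- Neonatal deaths added (20–40 per 1,000 live births), every loss excluded (f = 0.061 to 0.080): 3.1 to 4.0 points at r = 0 and 1.5 to 2.0 at r = 0.5.

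The r = 0 figures assume that no excluded woman used care. RR of 2 to 3 corresponds to r of about 0.4 to 0.6. For example, with L = 0.082 and RR = 3, SBA among losses is 0.33/2.34 = 14.1%, and 14.1/34.7 = 0.41. The r = 0.5 rows are therefore the ones comparable with the table.

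**Contrast between arms, if the rule is reused**

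For an observed 50% against 45%, the true difference is 0.50(1 − f₁(1 − r)) − 0.45(1 − f₀(1 − r)), with f₁ for intervention and f₀ for control, every loss excluded.

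| f₁ | f₀ | True difference, r = 0 | r = 0.5 |
|---|---|---|---|
| 4.2% | 4.2% | 4.8 | 4.9 |
| 3.0% | 4.2% | 5.4 | 5.2 |
| 4.2% | 8.0% | 6.5 | 5.75 |

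With equal losses, an observed 5.0 is close to the truth. With fewer losses under intervention, the observed 5.0 is too small.

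**The case against.** The strongest reply concerns scope. The rule appears only under Phase 1, and the sample size is tied to the formative survey. No section states eligibility for the midterm or end surveys. At baseline there is no selection after allocation. This stands, so the consequences for the trial comparison can be stated only conditionally.

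A reader might also infer that the rule removes the very perinatal deaths that objective 3 compares. The article does not support this. Study design and setting lists perinatal mortality as separate measures beside the utilization surveys, and nothing says it is estimated from this sample. The source and denominator are not given, but an article may leave that to the full protocol.

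A third tempting reading is that all bereaved mothers are dropped. The word living is not in the text, and mothers with another under-5 child stay eligible and are asked about births in the period. Quoting 33.9–34.7% as the expected distortion at 33% would ignore this.

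Finally, the primary outcome is SBA, and the level bias largely cancels between arms when losses are equal. No false-positive conclusion has been shown.

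These points narrow the concern without removing it. The eligibility rule is stated rather than omitted. A woman whose only recent delivery was a stillbirth does not, in ordinary language, have an under-5 child, and no provision brings her in.

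**Conclusion.** The concern holds as a limited selection bias in the Phase 1 survey. Some bereaved mothers are ineligible, and the article's own Background gives the direction: use of care reads too high. The size is about 0.1 to 0.8 points at 33% SBA, with an upper bound of 0.9 to 1.7 points if every loss were excluded. Only the 42 per 1,000 and the 33% come from the article; neonatal rate, relative risk and exclusion shares are assumed. For objective 1, the loss of non-users from the analysis matters more than the shift in the percentage.

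Reuse at midterm and end is plausible from the 725/725 split and the repeat surveys, but is not stated. If it happens and the intervention reduces deaths, the effect on use would tend to be diluted, and perinatal mortality could not be validly taken from this sample. Severity is minor to moderate. The figures do not support calling it a flaw that invalidates the trial comparison.

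**What to change.** Replace the under-5-child condition with any birth, live or still, within a stated recall window, regardless of whether the child is alive. Record the outcome of that birth in the existing computer-assisted form. State that the same rule applies in both arms at baseline, midterm and end.

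This does not require perinatal mortality to be taken from the survey. With 725 women per arm, one birth each and clustering ignored, power for an assumed 30% reduction from 6.2–8.2% would be only about 35–45%.

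The cost is one changed eligibility line and a few added questions. The downside is a slightly longer interview on a sensitive subject, for which interviewers need training. Mothers left out at baseline cannot be recovered in the analysis, so the change belongs before fieldwork. If baseline is already complete, the limitation should be reported with the bounds above, and any change of rule at later rounds should be made in both arms together.
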